### Client measures

#### Baseline

Immediately before receiving the initial CIL and/or brief advice intervention, participants will be invited by the Offender Manager to provide contact details and complete the Extended AUDIT [27], Euroqol (EQ-5D) [39], a short service use questionnaire (S-SUQ) [40] and modified Readiness Ruler [41]. Participants in the extended intervention will complete the baseline at the same stage as those in other groups.

AUDIT is normally used as a screening test for alcohol use disorders [27]. However in this context the AUDIT will be used as a means of establishing the severity of alcohol use disorders at baseline, in a way that is least intrusive to naturalistic aim of the trial in the probation setting and as a means of measuring the adequacy of matching between the intervention groups at baseline. The AUDIT contains 10 items to measure alcohol consumption, alcohol problems and dependence over, in this case, the previous 6 months, and the sum of the item scores provides a measure of severity which has been used in several previous studies, allowing comparability with other primary care samples [11]. We felt that the use of more elaborate baseline alcohol consumption measures would interfere with the naturalistic aims of the study and possibly would contribute a form of intervention in itself, so introducing bias into the evaluation of the interventions by reducing the difference between trial interventions. In addition, participants will complete the EQ-5D as a brief 5-item measure of quality of life [39]. Use of health, social criminal justice services and wider societal costs will be measured via a shortened version of Service Use Questionnaire [40] which allows estimation of health care and wider social costs for health economic analysis in the six months prior to intervention. A modified Readiness Ruler [41] containing a zero to ten scale of the extent to which participants think about their drinking as a problem or have addressed this issue will assess participants' motivational state regarding changing their drinking behaviour.

#### Follow-up

At 6 and 12 months after intervention, all participants will be contacted via telephone, post or email as preferred by research staff that will be blind to their intervention condition. Participants will be offered telephone, postal or face-to-face follow-up as preferred. Researchers will administer the shorter Alcohol Use Disorders Identification Test (Extended-AUDIT) [42]. Alcohol-related problems will be assessed via the brief Alcohol Problems Questionnaire (APQ) [43]. We will also re-administer an extended version of the Service Use Questionnaire SUQ [40], EQ-5D [39] and the modified Readiness Ruler [40]. Participant satisfaction with the advice/help received during the intervention will be assessed using a modified version of the Patient Satisfaction Questionnaire (short form) at 12 months [44].

At follow-up, each participants will also be asked if, and how often, they made use of the Drink-Line telephone number.

### Financial incentives

We propose to incentivise research participation in one of two ways dependent on individual offices choice. They will either receive via payments of £1,000 to each probation site geographical area subject to successful offender recruitment or the participating OMS will receive £20.00 of high street vouchers for each eligible case recruited.

### Participant incentives

Participants will receive a £10 retail voucher after completing the baseline research interview and a £10 voucher for completing each of the 6 and 12 month research follow-up interviews.

### Economic evaluation

The economic component of the study comprises a cost-effectiveness and cost-utility analysis. The study aims to identify, quantify and value resources related to alcohol screening and intervention by OMs in probation and the subsequent use of health, social care, and criminal justice services by offenders following each type of intervention. Resources utilised in the identification and brief intervention delivery or control condition will be recorded by OMs involved on an ongoing basis. This will allow the calculation of costs related to implementation of different models of screening and brief intervention. Local costs will be used to calculate the costs of the interventions, which will include staff costs, premises costs and costs of leaflets and other consumables. In addition, specific training costs for staff will be calculated, in terms of staff time, premises costs and the cost of training materials.

Offenders' self-reported use of health, social care and criminal justice services will be identified retrospectively using a short form of the service use questionnaire previously used to evaluate costs associated with interventions for alcohol use disorders [40] and applying a common set of national unit cost estimates. The economic analysis will calculate the incremental cost-effectiveness of the control condition with the AHW condition under study, using measures of clinical outcome and quality of life, EQ-5D [45] responses at baseline and at 6 and 12 months follow up. The use of EQ-5D enables the estimation of Quality Adjusted Life Years. Data will be bootstrapped to account for the expected skewness evident in economic cost data [46]. The analysis will include the construction of cost-effectiveness acceptability curves to illustrate the probability that the brief intervention is more cost-effective than usual care, based on different monetary values being attached to QALYs. The use of QALYs follows the recommendations of NICE and enables the value for money afforded by treatment to be compared to a range of other health care interventions. Furthermore, combination of the economic cost data and outcome data with offender data collected in the trial will enable a secondary analysis of various offender characteristics that may influence the cost-effectiveness of the intervention.

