## Objectives

The objectives of the trial are:

• To conduct a pragmatic multicentre cluster randomised controlled trial of screening and brief intervention for hazardous and harmful drinkers in typical probation settings in three English regions.

• To identify the most efficient methods for alcohol screening in typical probation settings.

• To compare the effectiveness and cost effectiveness of different models of brief intervention with an information leaflet in offenders with hazardous, harmful and dependent alcohol consumption.

• To assess the implementation of different screening and brief intervention approaches by Offender Managers (OMs) in typical probation practice.

• To identify attitudinal, practical, skill, resource, and reinforcing factors that predict successful implementation of screening and brief intervention in probation settings.

• To assess the relative impact of the different models of screening and brief intervention on uptake of alcohol services, including an alcohol helpline.

• To assess the relative impact of the three intervention strategies on reoffending.

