### Design

The trial will adopt a 2 × 3 nested factorial design encompassing screening method (the Fast Alcohol Screening Test (FAST) [28] or a modified Single Alcohol Screening Questionnaire (M-SASQ)) [29]) and brief intervention intensity (Client information leaflet (CIL); Brief advice (BA); Brief lifestyle counselling (BLC)). The main advantages of utilising a factorial approach are twofold. First each of the elements (screening tool and intervention) can be analysed independently with sufficient power to make meaningful interpretation of relative effectiveness. Second, the method enables meaningful interpretations of the relative effectiveness of any screening tool and intervention modality.

The 96 recruited OMs will be randomly assigned to 1 of 2 screening tools (48 OMs using each tool) and 1 of 3 intervention conditions (32 OMs in each condition) as shown in Table 1. Since we expect that there may be a difference in uptake of screening between intervention conditions, we expect the recruitment to take varying periods of time in the different conditions.

**Table 1 T1:** SIPS CJS trial design

	Intervention allocation				Total
		**PIL**	**BA**	**BLC**	
	
		OMs = 16	OMs = 16	OMs = 16	OMs = 48
**Screening allocation**	**FAST**	Participants = 80	Participants = 80	Participants = 80	Participants = 240
	
	**M-SASQ**	OMs = 16	OMs = 16	OMs = 16	OMs = 48
		Participants = 80	Participants = 80	Participants = 80	Participants = 240

		OMs = 32	OMs = 32	OMs = 32	OMs = 96
**Total**		Participants = 160	Participants = 160	Participants = 160	Participants = 480

The trial will incorporate cluster randomisation of OMs to avoid the risk of contamination. OMs trained to deliver brief advice become compromised in their ability to deliver alternative versions of such care; thus it is not practical for individual OMs to deliver both control and intervention conditions in this trial. Therefore OMs will consistently deliver one particular type of brief intervention.

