### Study Hypotheses

• Brief lifestyle counselling by an Alcohol Health Worker (AHW) is more effective and cost effective than simple structured advice conducted by OMs in a typical probation setting.

• Brief lifestyle counselling and simple structured advice are more effective and cost effective than a Client Information Leaflet (CIL).

• Access to referral to an AHW results in greater screening and intervention activity than training of probation staff in screening and brief intervention alone.

• Attitudinal, practical skill, resource, and reinforcing factors predict screening and intervention activity.

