### Brief lifestyle counselling

OMs randomised to deliver Brief Lifestyle Counseling, will be trained to screen eligible offenders for hazardous or harmful drinking. Offenders who screen positive and provide consent to participate in the study will complete the baseline questionnaire and will then receive up to five minutes of simple structured brief advice from trained OMS using the SIPS Brief Advice tool "Brief advice about alcohol risk". Offenders in this condition will also receive a Client Information Leaflet (CIL) at the end of the brief advice. OMs will also be trained to refer offenders to an AHW, by making an appointment usually the following day or as soon as possible after probation attendance. The AHW will be experienced in carrying out alcohol assessment and brief interventions. The AHW will deliver a 20 minute brief lifestyle counseling intervention to offenders who attend the appointment at the probation office, using the SIPS Brief Lifestyle Counselling (BLC) Tool which has been developed for the purpose of the SIPS programme. It is based on the "How much is too much?" Extended Brief Intervention tool developed as part of the UK version of the Drink-Less BI programme [31] from a prototype used as part of a World Health Organisation collaborative study on alcohol screening and brief intervention [32].

All intervention tools and protocols are available from the SIPS study website http://www.sips.iop.kcl.ac.uk.

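### The economic analysis names only leaflet against Alcohol Health Worker counselling, so two of the three hypothesised cost-effectiveness contrasts, both involving brief advice, have no stated analysis

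*Protocol article*

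**What the plan says.** The Design section sets up three intervention arms: CIL, BA and BLC. The Study Hypotheses attach a cost-effectiveness claim to every pair of them. The first says that BLC delivered by an AHW "is more effective and cost effective than simple structured advice conducted by OMs in a typical probation setting". The second reads "Brief lifestyle counselling and simple structured advice are more effective and cost effective than a Client Information Leaflet (CIL". The Objectives include the aim "To compare the effectiveness and cost effectiveness of different models of brief intervention with an information leaflet".

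The Economic evaluation section names one incremental comparison: "The economic analysis will calculate the incremental cost-effectiveness of the control condition with the AHW condition under study". Its acceptability curves are to show "the probability that the brief intervention is more cost-effective than usual care". The section on cost effectiveness of crime adds number of offences and time to failure as outcomes, but names no further contrast between arms.

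The section describing the BLC arm says that its participants "will then receive up to five minutes of simple structured brief advice from trained OMS using the SIPS Brief Advice tool". They also receive the leaflet and are then referred to the AHW for the 20-minute session.

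**The concern.** The sentence that fixes the economic comparison fits a two-arm trial; this trial has three arms with ranked hypotheses. No sentence in the article names an economic contrast involving BA. The acceptability curves do not fill the gap: they refer to a single brief intervention when there are two such arms, and to usual care, which is not the name of any arm.

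A probation service deciding whether to fund AHWs needs to know what the AHW session adds to five minutes of advice from an Offender Manager. BLC v CIL does not answer that, because it pools the effect and cost of the advice with those of the AHW session. If the contrasts are not fixed beforehand, the comparator reported for BLC could also be chosen after the results are known.

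**Working it through.** The plan states no cost, QALY difference or cost-effectiveness ratio, so there is no economic figure to reproduce. The check has three steps.

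**1. Hypothesised contrasts against named contrasts.**

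| Contrast | Hypothesised | Named in Economic evaluation |
|---|---|---|
| BLC v BA | Yes (first hypothesis) | No |
| BLC v CIL | Yes (second hypothesis) | Yes |
| BA v CIL | Yes (second hypothesis; also Objectives) | No |

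One of three is specified.

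**2. What each contrast measures.** From the Interventions section, CIL is the leaflet; BA is advice plus leaflet; BLC is advice plus leaflet plus referral to the AHW session. With C for mean cost and E for mean QALYs:

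- C(BLC) − C(CIL) = [C(BA) − C(CIL)] + [C(BLC) − C(BA)], and likewise for E.

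When both QALY steps are positive, the BLC v CIL ratio is the average of the BA v CIL and BLC v BA ratios, weighted by the QALY gained at each step. A single average does not determine its two components.

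**3. Illustration with assumed values.** Assume costs per client of £1 (CIL), £6 (BA) and £50 (BLC), a BLC gain over CIL of 0.010 QALY, and a BA gain g that varies from 0 to 0.010.

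- BLC v CIL = (50 − 1)/0.010 = £4,900 per QALY for every g.
- BA v CIL = (6 − 1)/g.
- BLC v BA = (50 − 6)/(0.010 − g).

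| BA gain g | BA v CIL | BLC v BA | BLC v CIL |
|---|---|---|---|
| 0 | BA dominated (£5 more, no gain) | 44/0.010 = £4,400 | £4,900 |
| 0.001 | 5/0.001 = £5,000 | 44/0.009 = £4,889 | £4,900 |
| 0.002 | 5/0.002 = £2,500 | 44/0.008 = £5,500 | £4,900 |
| 0.008 | 5/0.008 = £625 | 44/0.002 = £22,000 | £4,900 |
| 0.010 | 5/0.010 = £500 | BLC dominated (£44 more, no gain) | £4,900 |

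Check of the weighting at g = 0.008: 0.8 × 625 + 0.2 × 22,000 = 500 + 4,400 = 4,900.

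The crossover is where BA v CIL equals BLC v CIL: g = 5/4,900 = 0.00102, about 10% of the BLC gain, which matches BA's share of the added cost (5/49 = 10.2%). Below it, BA is dominated or extendedly dominated and BLC v CIL is the right increment. Above it, BLC v CIL understates the ratio for the AHW step.

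A second assumed set gives the same pattern. With added costs over CIL of £10 (BA) and £50 (BLC) and a BLC gain of 0.01 QALY, BLC v CIL is 50/0.01 = £5,000 throughout. BLC v BA is £4,000, £5,333, £8,000 and £16,000 when BA achieves 0%, 25%, 50% and 75% of the BLC gain; at 100% BLC is dominated.

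**The case against.** The strongest reply is that BA is inside the economic evaluation. The section plans to cost the different models and to record service use after each type of intervention. EQ-5D is collected from all participants at baseline, 6 and 12 months. The sentence at issue names one contrast without ruling out others. This stands as far as data are concerned: a reader might infer that BA is excluded from the economic work, or that the trial is incapable of testing its hypotheses, and the document supports neither. But collecting data for an arm does not specify a comparison that uses it.

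A second reply is that a condensed article leaves health-economic detail to a fuller plan. That holds for the mechanics, such as ordering arms by cost, applying dominance rules and plotting several options. It does not hold for the choice of contrast, because the article states one and that statement falls short of its own hypotheses.

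Third, a reader might infer that the first hypothesis goes wholly unanswered. It has an effectiveness half, which falls under the Planned analysis section; only the cost-effectiveness half lacks a named contrast. The BLC v CIL part of the second hypothesis is covered too. The Objectives support BA v CIL but not BLC v BA, since they compare the models with the leaflet; BLC v BA rests on the Study Hypotheses.

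Fourth, usual care is most naturally a loose label for the leaflet control. That is a correction of terms, not a separate flaw.

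**Conclusion.** The inconsistency is real. The Economic evaluation section specifies one of the three cost-effectiveness contrasts in the Study Hypotheses and omits both that involve BA. Because BLC includes BA, the value of the AHW session can be judged only through the BLC v BA contrast.

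The count of one in three and the structural argument need no outside figure. The monetary illustration rests entirely on assumed costs and gains. It shows that the stated contrast can stay fixed while the relevant one ranges from slightly lower to dominated, but it establishes neither the size nor the direction of any error in this trial. A reader might take one row, such as £22,000 against £4,900 (about 4.5-fold), as the size of the problem; that multiple depends on giving BA 80% of the BLC gain, for which the documents offer no support. Nor can one say that BLC would wrongly be judged cost effective, since the article gives no threshold value for a QALY.

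The point should be fixed, but it is not critical. It touches a secondary component and leaves the primary outcome, randomisation, sample size and data collection unaffected.

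**What to change.** Amend the Economic evaluation section, before outcome data are analysed, to state:

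- a fully incremental analysis of CIL, BA and BLC: order the arms by mean cost, remove dominated and extendedly dominated options, and derive ratios between the options that remain;
- that BA v CIL and BLC v BA are reported (with a statement of dominance where it applies), alongside the BLC v CIL contrast already planned, so that each hypothesised pair has an analysis;
- acceptability curves showing all three arms on one plot;
- the client information leaflet control named in place of usual care.

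The subsidiary analysis of offending outcomes should use the same contrasts. The cost is a change of wording and a little more analysis. No further participants or data are needed, as 160 participants per arm and the cost, service-use and EQ-5D data are already planned.

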### Cost effectiveness of crime

The economic analysis currently is designed to consider cost effectiveness in terms of incremental cost per QALY. However, one of the key outcomes of interest to criminal justice providers is re-offending. We will therefore use these additional data to undertake subsidiary cost-effective analysis and consider whether the choice of principal outcome measure alters the recommended decisions. The two outcomes chosen will be number of offences and time to failure and the analysis will be conducted on the sample participants with both QALY and CJS data.

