### Consent

Consent to participate will be obtained in a three- stage process. OMs will give every offender a copy of the Client Information Leaflet (CIL) to take away to read before the next appointment. At the next appointment, OMs will ask the client if they have read the leaflet and whether they have any questions. OMs will then establish verbal consent to confirm eligibility to take part, collect some basic demographic information and to be screened for an alcohol use disorder. Those who then are positive on the screening tool will have the study explained to them verbally by OMs and in writing (using the Client Information Leaflet). Written informed consent will be obtained by OMs. This will include permission to give the client's data and contact details to the research team, and provide the research team with access to the clients Police National Computer (PNC) and probation records, and to participate in follow up after 6 and 12 months. The research team will then contact the participant within two weeks to thank him/her for taking part in the study.

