### Sample size calculation

The sample size calculation is designed to account primarily for intervention level outcomes. Powering the study in this way will also account statistically for appropriate outcomes for screening approach and screening method. The primary outcome for this study is the proportion of offenders who are consuming alcohol within recommended levels at 6 and 12 month follow-up. Recent meta-analysis [19] suggests that the difference between brief intervention and control is of the order 13%, 5% reduction in the control group and 18% in the brief intervention group. In order to detect a difference of this magnitude at the 5% significance level with 80% power, for a 2-sided test, requires 109 offenders in each of the 3 groups, a total of 327. Our experience with other multi-centre randomised controlled trials of interventions for alcohol use disorders suggests that with assiduous follow-up the potential loss to follow-up across groups is of the order 25%. Taking this loss into accounts inflates the sample required to 145 in each group, a total of 435 offenders.

The proposed study involves a cluster design and requires a statistical adjustment to account for any potential cluster effect. The literature is unclear regarding an appropriate estimation of an intra-class correlation coefficient in this population. Our experience leads us to assume the ICC should be similar to primary care correlation coefficients, 0.04. Assuming a cluster size of the order 3 offenders this inflates the sample size calculation by a factor of 1.1 requiring 160 offenders in each group, a total of 480, with an expectation that at least 365 will be followed up at 12 months.

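### The subsidiary crime cost-effectiveness analysis is confined to participants who also have QALYs, so it selects on completed follow-up and sets aside offence records already consented to

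*Protocol article*

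**What the plan says.** The section *Cost effectiveness of crime* adds an analysis of re-offending to the main cost-per-QALY work. Its purpose is to "undertake subsidiary cost-effective analysis and consider whether the choice of principal outcome measure alters the recommended decisions". The effect measures are fixed: "The two outcomes chosen will be number of offences and time to failure". So is the analysis set: "the analysis will be conducted on the sample participants with both QALY and CJS data".

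Three other sections determine what that set contains.

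- *Economic evaluation* builds QALYs from "EQ-5D [45] responses at baseline and at 6 and 12 months follow up". For costs it says: "Offenders' self-reported use of health, social care and criminal justice services will be identified retrospectively using a short form of the service use questionnaire".
- *Consent* records that written consent at entry will "provide the research team with access to the clients Police National Computer (PNC) and probation records".
- *Sample size calculation* expects that "the potential loss to follow-up across groups is of the order 25" per cent, and plans for "a total of 480, with an expectation that at least 365 will be followed up at 12 months".

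**The concern.** The two kinds of data become available in different ways. A QALY exists only if the participant was reached and answered at follow-up. An offence count or a time to first offence can come from records, whether or not the person was ever reached again. Requiring both means that a follow-up contact, which happens after randomisation, decides who enters an analysis whose effect measure does not need that contact.

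In a probation population it is plausible, though the document does not say so, that people who re-offend or go into custody are harder to interview. Missing QALYs would then be related to the outcome under study, and the both-available sample would under-represent re-offenders. The analysis is meant to show whether switching from QALYs to crime outcomes changes the recommended option. If selection differed between arms, it could produce or hide such a change.

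**Working it through.** **Inputs from *Sample size calculation*:** 109 per group before inflation; 25% loss; ICC 0.04; cluster size about 3; 160 per group and 480 in total; at least 365 followed up at 12 months.

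**1. The plan's own figures.** The standard two-proportion formula with continuity correction, for 5% against 18%, two-sided 5% and 80% power, gives 109 per group as stated. Allowing for loss, 109 / 0.75 = 145.3 (stated as 145). The design effect is 1 + (3 − 1) × 0.04 = 1.08, which the plan rounds to 1.1. Then 145 × 1.1 = 159.5, rounded to 160, and 3 × 160 = 480. Expected follow-up is 480 × 0.75 = 360, close to the stated 365. The chain reproduces to within rounding, so either follow-up figure can be used.

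**2. Participants left out, if QALY completeness equals planned follow-up.**

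- From the stated 365: 480 − 365 = 115, and 115 / 480 = 24.0%.
- From the 25% loss: 480 − 360 = 120, and 120 / 480 = 25.0%.

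**3. Participants left out, if a QALY needs both the 6- and 12-month EQ-5D.** The article gives no 6-month figure. Assume 25% loss at each wave.

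| Overlap of the losses (assumed) | With both waves | Left out |
|---|---|---|
| Same people lost at both waves | 480 × 0.75 = 360 | 25% |
| Independent losses | 480 × 0.75² = 270 | 44% |
| No overlap | 480 × 0.50 = 240 | 50% |

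**4. Precision.** If the omitted people carried full information, standard errors in the restricted set would be larger by √(480 / 365) = 1.147 to √(480 / 360) = 1.155, about 15%, ignoring clustering. This is a ceiling on the gain: their self-reported costs would be imputed, not observed.

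**5. Can bias between arms be sized?** Take an assumed case with no true effect: 35% re-offend in each arm, and 55% among those lost. A proportion is used for simplicity; the planned outcomes are a count and a time. The rate among completers is (0.35 − loss × 0.55) / (1 − loss).

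| Loss | Completer rate |
|---|---|
| 20% | (0.35 − 0.110) / 0.80 = 30.0% |
| 25% | (0.35 − 0.1375) / 0.75 = 28.3% |
| 30% | (0.35 − 0.165) / 0.70 = 26.4% |

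With 25% loss in both arms the difference is zero. With 20% in one arm and 30% in the other it is 3.6 points. The article gives no loss by arm, so this shows a mechanism and not an expected size. In every row the completers' rate is below the true 35%, so under these assumptions the level of re-offending is understated even when the difference between arms is not.

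**The case against.** The other side has a good case on several counts.

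- **A common sample has a purpose.** The analysis asks whether the decision changes with the outcome. If the two outcomes were assessed on different people, a changed decision could simply reflect who was included. This stands, and any remedy must keep one common sample.
- **Costs are missing too.** *Follow-up* re-administers the service use questionnaire at the same 6- and 12-month contacts as EQ-5D. Most people without a QALY would also lack service-use costs, so offence records alone cannot bring them into a cost-effectiveness analysis. This stands for service use. It does not apply to screening and intervention resources, which *Economic evaluation* has offender managers record as they go.
- **The analysis is subsidiary, and missing-data methods are often left to a fuller document.** Both are true. But the article does more than leave the method open: it names a complete-case set.

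Some stronger readings are tempting and are not supported. A reader might infer that the trial's comparison of arms on re-offending is itself limited to QALY completers. It is not: that is a separate item under *Objectives*, and it can use everyone with records. A reader might also infer that intention to treat is abandoned. Participants stay in their allocated arm; this is a complete-case set, exposed to the same kind of follow-up loss that the plan expects for the primary outcome. Nor does the document establish that records exist for all 480: it gives consent to access, not completeness, and never says outright that CJS data means those records.

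**Conclusion.** The point holds as a minor one, confined to the crime cost-effectiveness analysis. The stated set conditions on completed follow-up and leaves out about 115 to 120 of 480 participants (24 to 25%), or up to half under the least favourable two-wave assumption. Offence records for these people should largely be obtainable.

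This rests on three assumptions: QALY completeness is close to the planned follow-up, CJS data means the police and probation records covered by consent, and those records are nearly complete. The link between re-offending and loss to follow-up is plausible but undocumented. It would be wrong to infer a bias of known size or direction between arms, or a recoverable precision gain of the full 15%. The first depends on differential loss, which is not given. The second ignores that the added participants' costs would be imputed.

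**What to change.** Redefine the sample for the crime cost-effectiveness analysis, and for the QALY analysis it is compared with, as all consented participants with criminal justice records. Multiply impute missing QALYs and self-reported costs on that sample. The imputation model should include the observed offence outcomes, baseline EQ-5D, baseline AUDIT, trial arm and offender manager. Both decisions are then still compared on the same people. Keep the both-available sample as a sensitivity analysis, and state that CJS data means the police and probation records if that is what is intended.

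No new data collection is needed. The cost is a little more analysis and reliance on a missing-at-random assumption for the imputed QALYs and costs. Including the observed offences makes that assumption easier to defend, because the likeliest driver of loss is then in the model.
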